## Abstract

Unilateral spatial neglect (USN) rehabilitation requires the development of new methods that can be easily integrated into conventional practice. The aim of the HEMISTIM protocol is to assess immediate and long-term recovery induced by an innovative association of left-side neck-muscle vibration (NMV) and anodal transcranial Direct Current Stimulation (tDCS) on the ipsilesional posterior parietal cortex during occupational therapy sessions in patients with left USN. Participants will be randomly assigned to four groups: control, Left-NMV, Left-NMV + sham-tDCS or Left-NMV + anodal-tDCS. NMV and tDCS will be applied during the first 15 min of occupational therapy sessions, three days a week for three weeks. USN will be assessed at baseline, just at the end of the first experimental session, after the first and third weeks of the protocol and three weeks after its ending. Our primary outcome will be the evolution of the functional Catherine Bergego Scale score. Secondary outcome measures include five tests that investigate different neuropsychological aspects of USN. Left NMV, by activating multisensory integration neuronal networks, might enhance effects obtained by conventional therapy since post-effects were shown when it was combined with upper limb movements. We expect to reinforce lasting intermodal recalibration through LTP-like plasticity induced by anodal tDCS.

## 1. Introduction

Unilateral spatial neglect (USN) is a perplexing neuropsychological syndrome that affects approximately 30% of stroke-affected individuals worldwide [1]. This syndrome results from hemispheric lesions in cortical structures (posterior parietal cortex, superior temporal gyrus, temporo-parietal junction, and less frequently frontal cortices), subcortical structures (thalamus, basal ganglia) or white matter fiber tracts (fronto-parietal pathways) [2,3], with a greater prevalence after right brain lesions rather than left ones (38% and 18%, respectively [1]). These brain networks are known to be involved in the construction of the spatial coordinate system of egocentric and allocentric references frames [4]. Therefore, damage to these networks can lead to USN in all space sectors: extra-personal, peri-personal and personal spaces. In concrete terms, this syndrome affects spatial awareness and is characterized by the inability to detect or respond to stimuli from the contralesional side of space without any dysfunction in the capture or transmission of sensory information to the central nervous system. These spatial disorders have disabling functional consequences that can be observed during activities of daily living such as reading, dressing, shaving, eating or getting from one place to another [5].

It is well established that USN is an independent factor associated with poor prognosis and functional outcome after stroke [6], and consequently, the rehabilitation of this syndrome is a challenging issue. Conventional rehabilitation of USN is mostly based on visual scanning training, the first developed method, which aims at better visual exploration toward the contralesional side [7]. The effectiveness of this “top–down” approach is based on the stimulation of attentional resources and requires patients to be aware of their impairment in order to actively correct it. However, since attentional capacities are often altered after stroke and especially in patients affected by USN [8], other rehabilitation methods, called “bottom–up” approaches, favor sensory manipulations either by deceiving the patient’s body perception (vestibular stimulation, optokinetic stimulation, neck muscle vibration), which is costless in terms of attentional resources, or through cognitive adaptation induced by visuo-haptic distortion (visual prisms) [9]. Both showed interesting results in early-phase rehabilitation [10,11]. Among these “bottom–up” techniques, neck muscle vibration (NMV) consists in applying a 80–100 Hz vibration on the skin over the upper fibers of one of the trapezius muscles, creating a proprioceptive illusion such that the body midline and surrounding space are perceived to be shifted to the stimulated side [12]. Some studies have shown a persistent reduction in USN symptoms thanks to left-side NVM [13,14]. For instance, Kamada et al. [15] showed that applying this illusory technique for 5 min right before an occupational therapy session optimized its beneficial effects as quantified by the conventional Behavioral Inattention Test (c-BIT) [16], a neglect-specific test battery, and the Functional Independence Measure (FIM) [17]. In addition, several studies suggest that combining different therapeutic approaches with converging effects may lead to the best benefits on USN [18,19]. Left-side NMV appears to be ideal for combination with other rehabilitation techniques, given its safety, simplicity of use, passive nature and particular therapeutic effects. USN reduction was shown to persist when NMV was coupled with visual scanning training [20] or applied in a visuo-haptic feedback context [21]. This feedback context was achieved through repeated reaching movements similar to the motor activities usually performed during patients’ conventional rehabilitation sessions. These results therefore support the interest of associating the left-side NMV technique simultaneously to rehabilitation sessions for left USN patients.

A third category of treatment, that can neither be classified as “top–down” nor “bottom–up”, based on non-invasive brain stimulation such as repetitive transcranial magnetic stimulation (rTMS) or transcranial direct current stimulation (tDCS), is used to modulate neuroplasticity by increasing (low-frequency rTMS or anodal tDCS) or decreasing (high-frequency rTMS or cathodal tDCS) cortical excitability [22]. Recent meta-analyses on USN showed a significant benefit of non-invasive brain stimulations when cortical excitability is increased in the ipsilesional hemisphere and/or decreased in the contralesional hemisphere [23,24]. Many studies using different modes and cortical localizations of tDCS, based on a low-amplitude electrical current, have shown its effectiveness in reducing motor and cognitive disorders after a stroke [25]. Conventionally, the two main modes of tDCS (anodal and cathodal) imply that the stimulation electrode (anode for anodal tDCS and cathode for cathodal tDCS, respectively, a-tDCS and c-tDCS) is positioned on the cortical area to be modulated, the reference electrode being placed remotely (for example on the supra-orbital area) [22]. For instance, a single a-tDCS session on the ipsilesional posterior parietal cortex (i-PPC) [26] or c-tDCS on the contralesional posterior parietal cortex (c-PPC) [27] was sufficient to induce a significant improvement on neuropsychological performances in left USN patients. Beneficial effects on USN lasting up to one week were obtained after applying a-tDCS or c-tDCS (respectively, on the i-PPC or the c-PPC) for three weeks during daily occupational therapy sessions [28]. A third mode of tDCS, referred to as dual or bi-hemispheric, involves placing the two electrodes on the cortex on either side of the midline, aiming at modulating simultaneously and oppositely the excitability of the two hemispheres [29]. This dual mode in a bi-parietal configuration has also been successful in reducing USN symptoms [30,31]. Other studies recently evaluated the efficacy of tDCS in association with “bottom–up” rehabilitation techniques (visual prisms [32] and optokinetic drift [33]). Làdavas et al. [32] showed that the well-established efficacy of prism adaptation for reducing USN symptoms [11], applied in this study by daily 30-min sessions for two weeks, was significantly magnified by a 20-min application of a-tDCS on the i-PPC before (10 min) and partially while wearing visual prisms (10 first minutes). Similarly, Turgut et al. [33] showed significant benefits lasting up to 6 days after applying a therapeutic protocol combining dual-tDCS (anode on the i-PPC and cathode on the c-PPC) and optokinetic drift for 20 min eight times over two weeks.

USN rehabilitation remains a public health issue in terms of patients’ independence and healthcare costs. One of its main challenges lies in offering therapeutic innovations that can be easily integrated into conventional practice [34]. NMV and tDCS appear to be easy-to-use techniques that could meet this core condition for the rehabilitation of USN. The aim of the present protocol study is to assess beneficial effects on USN, specifically on immediate and long-term functional outcomes and neuropsychological aspects of spatial recovery, induced by a combined treatment associating the left-side NMV technique and a-tDCS on the i-PPC during occupational therapy sessions in patients with left USN. Our hypothesis is that the increase in excitability of the lesioned hemisphere induced by a-tDCS will amplify the lasting beneficial effects of left-side NMV during conventional occupational therapy sessions.

## 2. Materials and Methods

This multicentric prospective randomized controlled superiority trial will focus on assessing the benefits of our therapeutic protocol on independence in daily life activities, neuropsychological aspects of different spatial components of USN (personal, extra-personal and representational neglect) and egocentric spatial perception assessments, using a mixed measurement design. The HEMISTIM protocol will take place in three neurological rehabilitation centers in Grand-Est and Provence-Alpes Côte d’Azur regions, France.

### 2.1. Ethical Consideration and Trial Registration

#### 2.1.1. Informed Consent

Our clinical trial will be conducted in accordance with the Declaration of Helsinki. Oral and signed informed consent will be requested by an investigator after patients have received oral and written information related to the study. Participants can revoke their consent at any time.

#### 2.1.2. Data Management

The data will be recorded in an observation book by the evaluator in charge of the patient, written in a case report form and stored according to French legislation. A data monitoring committee will not be necessary in this context of intervention with minimal risk and constraints and without major modification of patients’ usual care. The confidentiality of collected data will be ensured by pseudonymization. The final dataset will be owned by the trial sponsor and accessible to all investigators, according to French legislation.

#### 2.1.3. Trial Registration

This study protocol was registered on the clinicaltrial.gov registry: NCT05281302. The manuscript is in accordance with the SPIRIT guidelines (http://www.spirit-statement.org/) for reporting study protocols. It has already been validated by the scientific and ethics committee of Institut Régional de Médecine Physique et de Réadaptation of Nancy, and an application is currently underway with an independent national ethics committee under the number 2022-A01673-40.

### 2.2. Eligibility Criteria

Patients aged at least 18 years old and admitted in a post-stroke rehabilitation unit in the sub-acute phase (15 days to 6 months after the onset of stroke symptoms) will be eligible for the study. Patients with left USN subsequent to a first unilateral right hemispheric stroke will be included. The diagnosis of stroke will have to be confirmed by computed tomography or magnetic resonance imaging. Screening for USN will be performed by the c-BIT [16], a score ≤ 129 defining USN. Patients unable to give informed consent, pregnant women, patients with skin lesions on the areas for electrode placement or having history of metal-in-cranium injury, epilepsy, vestibulo-cochlear illness or cardiac pacemaker will not be included.

### 2.3. Materials

Vibratory stimulators (VibramoovPhysio^®^, Techno Concept, Manosque, France) will be fixed bilaterally on the skin over the belly of the trapezius muscles and fastened with straps. Only the left-side NMV vibrator will be activated at a frequency of 100 Hz and an amplitude of 300 μm for 15 min, alternating 150 s of stimulation and 30 s of pause five times, as in previous studies [21,35].

tDCS will be applied using an electrical stimulator (DC-STIMULATOR^®^, NeuroCare, Illmenau, Germany) through large saline-soaked sponge surface electrodes placed as follows: anode over the (right) i-PPC (P4 according to the International 10–20 EEG electrode placement system) and cathode over the left supraorbital region. Stimulation parameters were chosen according to Làdavas et al.’s study [32] (anodal, 2 mA amplitude for 20 min).

### 2.4. Design of the HEMISTIM Protocol

This study will take place during 7 weeks of a conventional 5-day rehabilitation (Monday to Friday) for each patient included in this study, as illustrated in Figure 1.

#### 2.4.1. Inclusion in Groups

The first week will allow us to include patients with left USN and to randomly assign them to four independent parallel groups (centralized randomization in a 1:1 ratio performed using a custom made algorithm on Matlab (MathWorks, Inc., Natick, MA, USA) by a blinded investigator: a control group receiving no additional treatment to conventional occupational therapy sessions and three experimental groups receiving in addition to the usual treatment either left-NMV, left-NMV + sham-tDCS or left-NMV + a-tDCS experimental treatments, administered by trained occupational therapists.

In these three experimental groups, each patient will be equipped with vibratory stimulators during conventional occupational therapy sessions taking place on Monday, Wednesday and Friday for three weeks from the second week on. The left-side NMV vibrator will be activated during the first 15 min of the occupational therapy session (lasting 45 min), as previously described [21,35]. In the two experimental groups receiving sham or a-tDCS, electrodes will be placed as described above. A continuous 2 mA current will be delivered for 20 min in the left-NMV + a-tDCS group, 5 min before (patients will be seated in a quiet room) and during the first 15 min of the occupational therapy session, simultaneously to the NMV stimulation. The current will be automatically turned off after 20 s in the left-NMV + sham-tDCS group, allowing the reproduction of the initial mild itching sensation at the beginning of active tDCS, thus ensuring that the patient stays blind to the activation status of the device. In the case of adverse events or unintended effects of trial interventions, the investigator who enrolled the patient will report its occurrence to the trial sponsor through a report form provided in the case report form.

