### 2.5. Sample Size Calculation

To determine the number of left USN patients to include, we sought to perform an a priori headcount calculation based on published work in the field. However, none of them have combined NMV and tDCS or used the CBS score as the primary endpoint. No a priori power calculation could therefore be performed, but we were inspired by the number of patients included in the works of Làdavas et al. [32] and Turgut et al. [33], both of whom used tDCS on USN patients, the former combined with visual prisms and the latter with optokinetic drift. These two studies included 30 and 32 patients, respectively, which were divided for the first in two groups of 11 patients and one group of 8, and for the second in two groups of 16 patients. Thus, we estimated that 48 patients would be necessary for our study, randomly and homogeneously distributed in each of the 4 groups. To ensure that the target number of patients is recruited, three neurological rehabilitation centers admitting each year a large number of patients meeting the inclusion criteria will be involved. We will verify a posteriori that the groups do not differ in sex, mean age, education, duration of illness, or baseline CBS scores, and that they have similar stroke locations.

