The perceptual effects of NMV are attributed to a non-specific activation of the contralateral hemisphere and the activation of vestibular neurons in the parieto-insular cortex [42]. These neurons with bilateral receptive fields participate in multisensory integration processes and internal representations of the position of the head and body in space [42]. Left-side NMV seems to counterbalance the egocentric representation deviation observed in USN patients through these central mechanisms [43]. The key question of persistent effects was addressed by Ceyte et al. [35], who showed that lasting post-effects were only present when left-side NMV was associated with upper limb self-activation, and these results were consistent with our previous case study on a USN patient [21]. Transferring our protocol directly into conventional rehabilitation sessions could further increase their benefits. Indeed, reaching toward a target, as it was performed in a visuo-haptic feedback context in our previous studies [21,35], is very similar to the motor activities performed during ecological upper limb rehabilitation sessions. Based on these findings, we assume that using this technique during occupational therapy sessions might enhance beneficial effects obtained by conventional rehabilitation without needing to add specific sessions as it is sometimes suggested. In addition, the positive impact expected from this initial protocol could be optimized by tDCS neuromodulation. Indeed, non-invasive brain stimulations are known to modulate cortical excitability and therefore seem an ideal tool to promote long-lasting neuroplasticity [44]. The duration, amplitude and polarity of excitability changes vary accordingly to current flow direction, current intensity and stimulation duration [45]. Neuronal excitability changes induced by tDCS are supposed to be mediated by processes which are similar to long-term potentiation (LTP) and depression (LTD), among others [45]. These neurobiological mechanisms could significantly favor the intermodal recalibration induced by our initial protocol [35,46]. Interestingly, neurobiological post-effects can be observed during minutes and up to several hours after the end of tDCS stimulation [47,48]. Lasting clinical benefits on USN were also shown [28,31] but not consistently, due in part to substantial protocol differences (stimulation duration and repetition, concurrent activity, time since brain lesion). This technique has already been used simultaneously to occupational therapy sessions with positive and lasting results [28]. Moreover, its association with “bottom–up” rehabilitation approaches is very promising in terms of potentiating their beneficial impact on USN [32,33]. Associating tDCS with our initial protocol therefore seems perfectly suited to attempt to induce or reinforce LTP-like activity-dependent plasticity and consequently lasting intermodal recalibration to improve clinical aspects of USN.

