
There are some inherent features of our study protocol that deserve cautious consideration. Particular attention will be directed to the phenomena of limb activation and motor extinction [36,37], since our protocol is designed around the performance of voluntary upper limb movements simultaneously to stimulation sessions in USN patients. Although it has been shown in the literature that the use of the contralesional arm in the neglected hemi-space significantly reduces the severity of USN [37], these patients generally have great difficulty in mobilizing it in the early post-stroke stages. Moreover, the simultaneous use of both upper limbs in the neglected hemi-space limits or even suppresses the previously observed beneficial effects [36,37] possibly by perceptual “overshadowing” of the contralesional arm movements by the ipsilesional ones, according to Robertson and North [37]. Therefore, the therapists will carefully avoid bimanual activities in the neglected hemi-space, but exercises will be allowed with the right upper limb instead of the left one if the latter is too impaired to effectively perform them in initial phases of rehabilitation. This gradual increase in task complexity is also intended to maintain high motivation levels. Other vigilance points will be taken into account. We will be watchful of population homogeneity, hence the need to include a sufficient number of patients. We will compare the evolution of each patient from baseline according to his affiliation group, given the possibility of inter-subject variability in responsiveness. In addition, the long-term effects of tDCS should be clarified, and its optimal targets for motor and spatial rehabilitation have not been sufficiently studied yet. There is also a risk of misuse or overuse of non-invasive stimulations. Finally, local rehabilitation teams will be coordinated for inter-site standardization of inclusion, occupational therapy tasks, test performance and stimulation tools use.

In conclusion, the originality of our study lies in this novel combination of non-invasive stimulation techniques with low attentional demands and their application during occupational therapy sessions, thus ideally complementing conventional rehabilitation. The results of our multimodal approach should also provide interesting data to reconsider hemi-spatial theories suggesting a dominant function of the right hemisphere or others supporting an “interhemispheric competition” model [49].

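### Time since stroke may vary from 15 days to 6 months across arms of 12, yet the article states no balancing on it and no adjustment for it, only an after-the-fact comparison without consequence

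*Protocol article*

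**What the plan says.** Section 2.2 of the protocol article admits patients "in the sub-acute phase (15 days to 6 months after the onset of stroke symptoms) will be eligible for the study". Section 2.4.1 will "randomly assign them to four independent parallel groups" by "centralized randomization in a 1:1 ratio performed using a custom made algorithm on Matlab"; no stratification or minimisation factor is named. Section 2.5 sets the total: "we estimated that 48 patients would be necessary for our study, randomly and homogeneously distributed in each of the 4 groups".

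The primary outcome is how the CBS evolves, followed to three weeks after treatment ends while conventional rehabilitation continues (Sections 2.4.2 and 2.4.3). Section 2.6 sets out two analyses: a mixed ANOVA with test period and treatment group as its only factors, and, if its assumptions fail, Friedman tests within groups with Kruskal–Wallis tests on change from baseline between groups. Neither contains a covariate.

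Time since stroke comes up at two other points. Section 2.5 promises: "We will verify a posteriori that the groups do not differ in sex, mean age, education, duration of illness, or baseline CBS scores". It does not say what follows if they do differ. The Discussion attributes inconsistent lasting benefit of tDCS partly to differences in "stimulation duration and repetition, concurrent activity, time since brain lesion". It adds: "We will be watchful of population homogeneity, hence the need to include a sufficient number of patients".

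**The concern.** The entry window is about twelve-fold wide (183/15 = 12.2), and the outcome is change over roughly six weeks of continuing rehabilitation. If expected change without study treatment depends on time since stroke, arms of 12 that differ by chance on it will also differ in expected change. Measuring each patient against his or her own baseline does not remove a difference in expected change.

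The contrast that isolates active tDCS compares 12 patients with 12. The article recognises the variable as important, but uses it neither at allocation nor in the analysis. The comparison it does plan comes after allocation is complete and leads to no action. If that comparison is non-significant, the report may say that the groups were verified as equal when they were not.

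**Working it through.** **Inputs from the article.** Entry at 15 days to 6 months, taken as 15 to 183 days (Section 2.2); four arms with equal allocation (Section 2.4.1); 48 patients (Section 2.5), so 48/4 = 12 per arm. Section 2.5 states that no power calculation was possible, so there is no effect size or SD to reproduce. For scale, 12 per arm gives 80% power at two-sided 0.05 for a standardised two-arm difference of (1.960 + 0.842) × √(2/12) = 1.14.

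**Assumptions, since the article gives no figures.** Entry times are either uniform over 15–183 days or early-weighted, 15 + 168 × Beta(1,3). Untreated change falls exponentially with time since stroke (60-day constant) and explains 10%, 25% or 50% of the variance in change. There is no treatment effect. The results come from 40,000 simulated trials of 4 × 12. A one-way ANOVA on a change score stands in for the group comparison, and a four-group ANOVA on time since stroke stands in for the planned balance check, whose method is not stated.

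**Step 1: size of chance imbalance.** The SD of entry time is 168/√12 = 48.5 days (uniform) or 168 × √(3/80) = 32.5 days (early-weighted). The standard error of a two-arm difference in means is SD × √(2/12).

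| | Uniform | Early-weighted |
|---|---|---|
| SE of a two-arm difference | 19.8 days | 13.3 days |
| A given pair differs by > 30 days | 13% | 2.4% |
| Some pair differs by > 30 days | 43% | 10.7% |
| Some pair differs by > 40 days | 18% | 1.4% |
| Median gap between the extreme arms | 28 days | 18 days |
| Balance test non-significant when some pair differs by > 30 days | 88% | 58% |

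**Step 2: what the planned check misses.** The share of all trials with a gap over 30 days that the test does not flag is 0.43 × 0.88 = 38% (uniform) or 0.107 × 0.58 = 6% (early-weighted).

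**Step 3: effect on the test.** Overall type I error without adjustment is 4.8–5.3% in every scenario, so it is not inflated. Given a gap over 40 days, the false-positive rate is 7–14% (uniform) or 9–37% (early-weighted), rising with the variance explained. The early-weighted range describes a rare event: 0.013875 × 40,000 = 555 simulated trials.

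**Step 4: precision.** If time since stroke explains a share R² of the variance in change, adjustment multiplies the residual variance by 1 − R². That is worth up to 1/(1 − R²) times the patients: 1.11, 1.33 and 2.00 for R² of 10%, 25% and 50%, before a small loss of degrees of freedom. An imbalance of one standard error on the recovery predictor shifts a two-arm contrast by √R² × √(2/12) = 0.13, 0.20 or 0.29 SD of change.

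**Step 5: with the fix.** Two strata split at the median, with 6 per arm in each, reduce the standard error to 9.9 days (uniform) or 7.9 days (early-weighted). The chance that some pair differs by more than 30 days falls to 1.1% or 0.1%. ANCOVA on log days since stroke holds type I error at 4.9–5.1% overall and at 4.7–5.8% in trials with a gap over 40 days.

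**The case against.** Simple randomisation with a concurrent control arm is valid, and chance imbalance is already allowed for in the 5% level. A reader might infer that natural recovery will pass for a treatment effect, or that the design is biased. Step 3 does not support that: on average there is no inflation, and only a trial that turns out badly imbalanced has a raised error rate. This part of the objection stands.

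A reader might also infer that the randomisation ignores time since stroke. A condensed article cannot show that, because the algorithm may contain a factor that is not reported. Only the absence of a stated factor can be claimed. The analysis is different: both versions are spelled out, neither adjusts, and the balance check is written down without a consequence. Followed as written, they would leave an imbalance uncorrected even in a trial where it is large.

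A further objection is that baseline CBS may carry most of the information. That is fair. Expressing the effect in CBS points with an exponential recovery curve would not answer it. With a 60-day constant, gain over 42 days is 1 − exp(−42/60) = 50.3% of current severity at every entry time, so baseline CBS would absorb the whole timing effect. Every patient must also have current neglect to enter, so late entrants are not an unselected recovering cohort. How much time since stroke adds beyond baseline CBS cannot be told from the article. The stated between-group analyses do not use baseline CBS as a covariate either.

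Finally, a reader might want lesion site balanced too, because the anode lies over the posterior parietal cortex. The article gives neither the frequency of parietal involvement nor evidence that it alters recovery or response, so that extension is not supported.

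**Conclusion.** The point holds as a matter of precision and of protection against a misleading estimate in the one trial that will be run. It does not hold as a claim of bias or of inflated overall error. The wide window, the arms of 12, the absence of a covariate and the check without consequence are all in the text. The size rests on assumptions: the chance of a gap over 30 days between some pair of arms is 43% or 10.7% depending on the entry distribution, and the gain from adjustment depends on how much of the variance in change is explained. The weakness of the planned check holds under both distributions, since it misses more than half of such gaps. With 12 per arm and a detectable difference of about 1.14 SD, a nearly free gain in precision should not be left unused.

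**What to change.** 1. In Section 2.6, pre-specify days since stroke (log scale) and baseline CBS as covariates in the CBS analysis of the post-treatment scores, so that the baseline CBS moves from a level of the period factor to a covariate.
2. Replace the Kruskal–Wallis test on change, as fallback for the CBS, with a method that accepts covariates, for example rank-based ANCOVA.
3. In Section 2.4.1, have the existing central algorithm stratify, or minimise with a random element, on time since stroke in two categories. Fix the cut before recruitment, near the expected median entry time. If the algorithm already does this, say so.
4. Keep the comparison in Section 2.5 as description only, without a claim that groups have been verified as equal.

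The cost is one or two degrees of freedom and a slightly more complex allocation. Time since onset has to be known to establish eligibility, and the CBS is already measured at baseline, so no new data are needed. Item 3 helps only patients not yet allocated; items 1 and 2 can still be adopted at any time before outcome data are examined.
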